### Randomization and blinding

2.4

All participants were randomly assigned in a 1:1 ratio to either the real acupuncture group (*n* = 33) or the sham acupuncture group (*n* = 33). Block randomization was applied, with a block size of four. The random allocation sequence was generated using SPSS Statistics (version 26.0) by an independent statistician who was not involved in clinical implementation or outcome assessment. Allocation concealment was ensured using sequentially numbered, opaque, sealed envelopes. After participants met the eligibility criteria and provided written informed consent, an independent researcher opened the envelopes sequentially to assign participants to the corresponding groups. This trial is designed as a double-blind, randomized controlled trial, with participants, acupuncturists, outcome assessors, and statisticians all blinded to treatment allocation. All procedures will be performed in accordance with predefined standard operating procedures (SOPs).

The acupuncture devices used in this trial were specifically designed and developed by the [name] PD Research Team (Figure 2). The disposable double-blind acupuncture device comprises a fixed blind-spot component and a needle body, and is available in four configurations based on skin penetration and insertion angle: real or sham needles with either vertical or oblique insertion. The real and sham needles are identical in external appearance, featuring an opaque design to prevent visual differentiation. The fixed blind-spot component is gourd-shaped and equipped with a custom adhesive base, allowing stable attachment to the skin surface. For real acupuncture, the needle tip is sharp, and a small slit at the bottom of the fixed blind-spot component allows the needle body (diameter × length: 0.35 × 50 mm or 0.35 × 65 mm) to penetrate the skin and elicit the intended acupuncture effect. In contrast, the sham needles have blunt tips and shorter needle bodies (0.35 × 42 mm or 0.35 × 36 mm), preventing skin penetration. However, the sham needles are sufficiently long to produce a mild pain, thereby maintaining participant blinding. In addition, a friction mechanism within the fixed blind-spot component provides resistance during insertion, preventing acupuncturists from distinguishing real from sham needles and thereby ensuring operator blinding. To evaluate the preliminary feasibility of operator blinding, a pilot validation test was conducted prior to the main trial. Ten acupuncturists with over 2 years of clinical experience performed the procedures and were asked to guess the needle type (real, sham, or uncertain). The distribution of responses did not suggest a clear ability to reliably distinguish between real and sham needles. Although limited by the small sample size, these findings provided preliminary support for the feasibility of operator blinding.

**Figure 2 fig2:**
[figure not shown]
The disposable double-blind acupuncture device.

The acupuncture device used in this trial has been granted a Chinese utility model patent (Patent No. 202520263962. X) and will be manufactured by a qualified company (laozongyi Co., Ltd.). Outcome assessors and statisticians will remain unaware of group allocation throughout the trial to minimize assessment and analysis bias. The success of blinding will be assessed after completion of the intervention by asking participants and acupuncturists to guess the allocated treatment group, and the distribution of responses will be compared with chance levels. To formally and quantitatively evaluate blinding success over the course of the trial, Bang’s Blinding Index (BBI) will be utilized. Within 5 min after the first treatment session and at the completion of the final session, both participants and acupuncturists will be asked to guess the group allocation (real, sham, or uncertain). The BBI will then be calculated to statistically assess the success and direction of blinding for both patients and practitioners.

### Intervention

2.5

#### Real acupuncture group

2.5.1

Participants allocated to the real acupuncture group will receive standard antiparkinsonian pharmacotherapy in accordance with the Chinese Guidelines for the Treatment of Parkinson’s Disease (Fourth Edition) (Chen, 2020). During the treatment period, participants will maintain their baseline antiparkinsonian medication regimen. Any necessary adjustments in medication dosage or regimen will be documented in detail in the case report forms (CRFs). In addition, all participants will be advised to follow a Mediterranean-style diet with a high fiber content (Portugal-Nunes et al., 2021). Dietary adherence will be monitored at each treatment visit through patient interviews, and dietary recommendations will be reinforced as needed to ensure compliance. On this basis, participants will undergo real acupuncture treatment at a frequency of three sessions per week, with each session lasting 30 min, for four consecutive weeks. The acupuncture prescription consists of Sishen Needles and the Intestinal Three-Needle (Tianshu [ST25], Guanyuan [CV4], and Shangjuxu [ST37]) (Table 1; Figure 3). The anatomical locations of all acupoints will strictly follow the National Standard of the People’s Republic of China (GB/T 1236–2021) (Xiaodong and Longxiang, 2022). All acupuncture procedures will be performed by licensed acupuncturists who have received standardized training and have at least 2 years of clinical experience in acupuncture practice.

**Table 1 tab1:** Location of acupoints used in this trial.

Acupoints	Location
Sishen needles	Four acupoints are located 1.5 B-cun anterior, posterior, and lateral to Baihui (GV20).
Tianshu (ST25)	On the upper abdomen, 2 B-cun lateral to the centre of the umbilicus.
Guanyuan (CV4)	On the lower abdomen, 3 B-cun inferior to the centre of the umbilicus, on the anterior median line.
Shangjuxu (ST37)	On the anterior aspect of the leg, on the line connecting ST35 with ST41, 6 B-cun inferior to ST35.

**Figure 3 fig3:**
[figure not shown]
The illustration of acupoints used in this trial.

#### Sham acupuncture group

2.5.2

Participants in the sham acupuncture group will receive the same standard antiparkinsonian pharmacotherapy and identical dietary counseling as those in the real acupuncture group. The only difference between the two groups lies in the acupuncture intervention. In the sham acupuncture group, needles will be applied without skin penetration. The selected acupoints, treatment frequency, session duration, and total number of sessions will be identical to those used in the real acupuncture group. Sham acupuncture procedures will follow the same procedural protocols to ensure consistency across groups.

### Emergency treatment

2.6

Participants will be permitted to use rescue emergency treatment if they experienced no complete spontaneous bowel movements for more than three consecutive days, or developed intolerable symptoms related to constipation, such as abdominal distension. Rescue medications included oral lactulose solution or glycerin enema. Each use of rescue treatment was fully documented in the CRFs. Bowel movements occurring within 24 h after rescue treatment will not be included in the calculation of weekly complete spontaneous bowel movements (CSBMs) or weekly spontaneous bowel movements (SBMs).

### Outcomes assessment

2.7

Outcome evaluation primarily focused on two domains: constipation severity and other PD-related outcomes. Clinical scale assessments and the collection of fecal and blood samples were conducted at three time points: pre-treatment (baseline), after week 4 of the treatment period, and at week 4 of the follow-up period (Table 2). All assessments and biospecimen collections were performed during the participants “on” medication state at each visit. Outcome assessors received standardized training and remained blinded to group allocation throughout the trial.

**Table 2 tab2:** Details of the planned visit schedule.

Task	Baseline period	Treatment period				Follow-up period
	Week 0	Week 1	Week 2	Week 3	Week 4	Week 8
Enrollment						
Informed consent	√					
Random assignment	√					
Demographic characteristics	√					
Intervention						
Real acupuncture		√	√	√	√	
Sham acupuncture		√	√	√	√	
Assessments						
CCS	√				√	√
CSBMs and SBMs	√				√	√
BSS	√				√	√
UPDRS	√				√	√
SCFAs	√				√	√
HDAC1 and pS129-α-syn	√				√	√
Blinding assessment		√			√	
Safety						
Adverse events		√	√	√	√	√

#### Primary outcome

2.7.1

The Chronic Constipation Severity Score (CCS) was used as the primary outcome measure to quantify constipation severity. The CCS evaluates eight dimensions of constipation, including bowel movement frequency, degree of defecation difficulty, sensation of incomplete evacuation, presence of abdominal pain or bloating, maximum time required for each defecation episode, use of defecation assistance, frequency of unsuccessful defecation urges within 24 h, and duration of constipation. Total scores range from 0 to 30, with higher scores indicating more severe constipation symptoms (Higashimori et al., 2021). To provide a clinically interpretable anchor for treatment response, a reduction of ≥5 points from baseline in the CCS was prespecified as a threshold for clinically meaningful improvement based on previous studies in neurogenic and refractory constipation populations (Kumar et al., 2017; Preziosi et al., 2011). However, we acknowledge that a universally established MCID for PD-related constipation is currently unavailable.

#### Secondary outcomes

2.7.2

##### Weekly CSBMs and SBMs

2.7.2.1

CSBMs were defined as bowel movements occurring without laxatives or manual assistance and accompanied by a sensation of complete evacuation. SBMs were defined as bowel movements occurring without laxatives or manual assistance, regardless of completeness. Lower weekly frequencies indicate greater constipation severity.

##### Bristol Stool Scale (BSS) score

2.7.2.2

Stool consistency was evaluated using the Bristol Stool Scale (BSS), which classifies stool form into seven types, ranging from separate hard lumps (Type 1) to watery stools (Type 7) (Lai et al., 2023).

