**Methods:**

This randomized controlled clinical trial will enroll 66 patients with PD–related constipation and randomly assign them in a 1:1 ratio to the real acupuncture group or the sham acupuncture group. Participants, acupuncturists, outcome assessors, and statisticians will be blinded to group allocation. The 8-week trial consists of a 4-week treatment period followed by a 4-week follow-up period. The primary outcome is the longitudinal change in the Chronic Constipation Severity Score (CCS) over time. Secondary clinical outcomes include weekly complete spontaneous bowel movements (CSBMs), spontaneous bowel movements (SBMs), Bristol Stool Scale (BSS) scores, and Unified Parkinson’s Disease Rating Scale (UPDRS) scores. In addition, exploratory outcomes include levels of short-chain fatty acids (SCFAs), histone deacetylase 1 (HDAC1), and phosphorylated *α*-synuclein at serine 129 (pS129-α-syn) measured in biofluid samples. Adverse events will be systematically monitored throughout the trial. The study is conducted in accordance with the SPIRIT guidelines.

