## Quality control, data management, and monitoring

3

All data will be recorded by investigators or outcome assessors using CRFs, while patient-reported outcomes (e.g., Weekly CSBMs, SBMs and BSS score) will be collected using paper-based diaries. To ensure data accuracy and completeness, all CRFs and paper diaries will undergo independent secondary verification by designated quality control personnel. An independent monitoring committee from the coordinating institution will conduct regular audits throughout the trial. These audits will include source data verification of CRFs and random contact with a subset of participants to confirm the authenticity and consistency of recorded information. All source documents, including patient diaries and CRFs, will be maintained in a complete, timely, legible, and traceable manner in accordance with Good Clinical Practice (GCP) guidelines. Any corrections to the recorded data will not obscure the original entry; instead, amendments will be documented with a written explanation, dated, and signed by the responsible investigator. Only CRFs and verified diaries reviewed and approved by the clinical monitor will be eligible for data entry. A designated data manager will oversee data entry and management. To ensure data integrity, double data entry will be independently performed by two trained personnel, followed by cross-validation and resolution of discrepancies before database lock. All trial data will be securely stored with restricted access, and the database will be locked only after completion of all data queries and quality checks.

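### The 24-hour post-rescue exclusion covers weekly CSBMs and SBMs but not the Bristol stool score, so stools produced by rescue treatment can enter that secondary outcome

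*Protocol article*

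**What the plan says.** - **Rescue (section 2.6).** "Rescue medications included oral lactulose solution or glycerin enema". Rescue is permitted after more than three consecutive days without a complete spontaneous bowel movement, or for intolerable constipation symptoms. Each use is documented in the case report form.
- **Exclusion rule (section 2.6).** Bowel movements in the 24 hours after rescue "will not be included in the calculation of weekly complete spontaneous bowel movements (CSBMs) or weekly spontaneous bowel movements (SBMs". No other outcome is listed.
- **Definitions of the counts (section 2.7.2.1).** "SBMs were defined as bowel movements occurring without laxatives or manual assistance, regardless of completeness". The CSBM definition carries the same laxative-free condition.
- **BSS (section 2.7.2.2).** It is a scale of seven types, "ranging from separate hard lumps (Type 1) to watery stools (Type 7". No condition on laxatives or rescue is attached.
- **Source (section 3).** The article says that "patient-reported outcomes (e.g., Weekly CSBMs, SBMs and BSS score) will be collected using paper-based diaries".
- **Timing (Table 2).** BSS is assessed at baseline, week 4 and week 8, alongside CSBMs and SBMs.

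**The concern.** Three secondary measures come from one diary, and two of them are protected from stools that rescue produced. An enema-induced stool is barred from the SBM count, yet nothing stops its form from being scored.

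This matters for the comparison between arms because rescue is not random. Its trigger is the symptom under treatment, so an effective treatment should lower its use. Stool form in the arm with more rescue would then partly reflect lactulose or enema. If that is the sham arm, its stools look softer and a true difference in stool form shrinks or reverses. If it is the real acupuncture arm, the distortion runs the other way.

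Change from baseline is exposed as well. The inclusion criteria (section 2.2.1) bar medication affecting gastrointestinal function for one month before treatment, so baseline BSS should be largely laxative-free. BSS at weeks 4 and 8 need not be.

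**Working it through.** **Plan figure.** The article gives no figure for BSS. Its one computable figure, the total of 66 in section 2.3, concerns CCS. It reproduces: difference 12.36 − 8.79 = 3.57; pooled SD √((4.63² + 4.26²)/2) = 4.449; 26 per arm by a two-sample t-test at 80% power; 26/0.80 = 32.5, rounded up to 33 per arm, 66 in total. Nothing below changes it.

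**The passages side by side**

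| Outcome | Diary source (section 3) | Defined as laxative-free (section 2.7.2) | 24-hour exclusion (section 2.6) |
|---|---|---|---|
| CSBMs | yes | yes | yes |
| SBMs | yes | yes | yes |
| BSS | yes | not stated | not stated |

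Followed literally, SBM and BSS are scored on different sets of stools from the same week.

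**Illustration of size.** All inputs are assumptions. It also assumes that individual stools are typed and averaged, which the article does not say. Let *b* be the mean type of spontaneous stools, *r* the type of post-rescue stools, and *f* the share of recorded stools that follow rescue.

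1. Mean within an arm: (1 − *f*)·*b* + *f*·*r*. The shift caused by rescue is *f*·(*r* − *b*). With *b* from 2 to 3, *r* from 5 to 7 and *f* from 10% to 30%:
   - smallest shift: 0.10 × (5 − 3) = 0.2
   - largest shift: 0.30 × (7 − 2) = 1.5
2. Shift between arms (real minus sham), with the same *b* in both: (*f*_real − *f*_sham)·(*r* − *b*). With *b* = 2.5, *f*_real = 10% and *f*_sham = 30%:
   - *r* = 5: −0.20 × 2.5 = −0.5
   - *r* = 6: −0.20 × 3.5 = −0.7
   - *r* = 7: −0.20 × 4.5 = −0.9
   
   With *f*_sham = 20% the range is −0.10 × 2.5 = −0.25 to −0.10 × 4.5 = −0.45. With equal shares the shift is zero, and with the shares swapped the sign reverses.
3. Masking. Suppose spontaneous stools average 3.0 (real) and 2.5 (sham), a difference of +0.5, with the 10% and 30% shares and *r* = 6:
   - real: 0.90 × 3.0 + 0.10 × 6 = 3.30
   - sham: 0.70 × 2.5 + 0.30 × 6 = 3.55
   - difference: −0.25, so the ordering of the arms reverses.

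**The case against.** **The rule's silence is not an inclusion.** The article never says that post-rescue stools are scored for BSS, and a full protocol or analysis plan may settle it. This stands in part, and it is why the point says that such stools can enter. It does not dispose of the point. The article did not leave post-rescue handling to another document: it stated the exclusion and listed the outcomes it covers, and BSS is not among them.

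**The sizes are invented.** They depend on assumed stool types, assumed rescue shares and an assumed averaging rule. That is correct. They show the mechanism and a plausible order of size, and do not estimate bias in this trial.

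**The direction is unknown.** Also correct. It depends on which arm uses more rescue, and equal use leaves no shift between arms in the simple calculation.

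**A stronger reading that the text does not support.** Because the abstract speaks of "Bristol Stool Scale (BSS) scores" and section 4 sends repeated measures to linear mixed models, a reader might infer that BSS is analysed as a continuous score where higher is better, so that loose stools count as improvement and Types 6 and 7 rank as the best result. Section 2.7.2.2 gives no direction of benefit, and section 4 does not assign BSS to any method. Direction and summary measure may sit in the analysis plan, which is not shown, so their absence is not part of this finding.

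**Conclusion.** The point holds in a limited form. The 24-hour exclusion is stated, is confined to CSBMs and SBMs, and leaves a third outcome from the same diary open to stools produced by rescue. Because rescue use depends on constipation severity, this is a plausible source of bias between arms; more rescue under sham would tend to hide a benefit.

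Under the assumed inputs the shift is 0.2 to 1.5 types within an arm, and 0.5 to 0.9 types between arms when 10% and 30% of stools follow rescue. The real size is unknown, and it is zero in that calculation if rescue shares are equal. The consequence is minor: BSS is one of several secondary outcomes, and neither the primary CCS analysis nor the total of 66 is touched.

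**What to change.** Extend the existing 24-hour post-rescue exclusion to BSS, so that stool form is scored on the same spontaneous stools as SBM. Report BSS on all recorded stools as a sensitivity summary. The rescue rule itself does not change.

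The cost is a line of analysis wording. Rescue uses are already documented in the case report form, and the CSBM and SBM rule already needs the timing of stools relative to rescue. One check is needed: that the diary ties each stool's type to its time, which the article does not state. The downside is that fewer stools contribute per week, and a participant whose recorded stools all follow rescue would have no BSS for that week. The all-stool summary shows whether that matters.

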##### Unified Parkinson’s Disease Rating Scale (UPDRS)

2.7.2.3

Parkinson’s disease severity was assessed using the Unified Parkinson’s Disease Rating Scale (UPDRS), a widely used clinical instrument that consists of four parts (I–IV) assessing mentation, activities of daily living, motor examination, and complications. Higher total scores reflect greater disease severity.

#### Exploratory outcomes

2.7.3

As the study was not formally powered for mechanistic biomarker endpoints, all analyses involving these biomarkers were predefined as strictly exploratory and hypothesis-generating.

##### Short-chain fatty acids (SCFAs)

2.7.3.1

Fecal samples were collected and stored at −80 °C within 5 h of collection. Concentrations of SCFAs were quantitatively analyzed using an ultra-performance liquid chromatography–tandem mass spectrometry (UPLC–MS/MS) system.

##### Histone deacetylase 1 (HDAC1) and phosphorylated *α*-synuclein at serine 129 (pS129-*α*-syn)

2.7.3.2

Fecal and blood samples were collected and processed immediately after collection. Blood samples were centrifuged at 3,000 ×*g* for 15 min at 4 °C to obtain cell-free serum. Fecal samples were homogenized in phosphate-buffered saline (PBS, pH 7.4) and centrifuged at 12,000 ×*g* for 20 min at 4 °C to obtain clarified supernatants free of cellular debris. The resulting supernatants were aliquoted and stored at −80 °C until analysis.

The concentrations of histone deacetylase 1 (HDAC1) and phosphorylated *α*-synuclein at serine 129 (pS129-α-syn) were measured using commercially available enzyme-linked immunosorbent assay (ELISA) kits according to the manufacturers’ instructions. The HDAC1 assay was performed using a human HDAC1 ELISA kit (Cat. No. JL20104-96 T; Jianglai Biotechnology, Shanghai, China), and the pS129-α-syn assay was performed using a human phosphorylated α-synuclein (Ser129) ELISA kit (Cat. No. H712234-96 T/EA; Macklin Biochemical, Shanghai, China).

Optical density was measured at 450 nm using a multimode microplate reader, and protein concentrations were calculated according to standard curves following the manufacturers’ instructions.

#### Blinding assessment and safety monitoring

2.7.4

To assess the success of blinding, participants and acupuncturists will independently indicate whether they believe the intervention was real or sham acupuncture after the first treatment session and at the completion of the final session. Their responses will be recorded using a standardized blinding assessment form and analyzed using BBI and descriptive statistics to assess the effectiveness of the blinding procedure.

Safety monitoring will focus on adverse events (AEs) related to acupuncture. All AEs will be recorded in standardized case report forms, including time of onset, duration, severity, suspected relationship to the intervention, actions taken, and clinical outcomes. AEs will be graded and their causality assessed in accordance with the Record Specification on Adverse Events in Clinical Trials of Acupuncture and Moxibustion (T/CAAM 0002-2022), ensuring a standardized and objective evaluation framework for acupuncture interventions (Moxibustion CAoAa, 2022). All AEs will be reviewed in a timely manner and reported to the Ethics Committee of the First Affiliated Hospital of Guangzhou University of Chinese Medicine in line with institutional and regulatory requirements. Serious adverse events (SAEs) will be reported immediately and managed according to predefined safety management protocols.

## Quality control, data management, and monitoring

3

All data will be recorded by investigators or outcome assessors using CRFs, while patient-reported outcomes (e.g., Weekly CSBMs, SBMs and BSS score) will be collected using paper-based diaries. To ensure data accuracy and completeness, all CRFs and paper diaries will undergo independent secondary verification by designated quality control personnel. An independent monitoring committee from the coordinating institution will conduct regular audits throughout the trial. These audits will include source data verification of CRFs and random contact with a subset of participants to confirm the authenticity and consistency of recorded information. All source documents, including patient diaries and CRFs, will be maintained in a complete, timely, legible, and traceable manner in accordance with Good Clinical Practice (GCP) guidelines. Any corrections to the recorded data will not obscure the original entry; instead, amendments will be documented with a written explanation, dated, and signed by the responsible investigator. Only CRFs and verified diaries reviewed and approved by the clinical monitor will be eligible for data entry. A designated data manager will oversee data entry and management. To ensure data integrity, double data entry will be independently performed by two trained personnel, followed by cross-validation and resolution of discrepancies before database lock. All trial data will be securely stored with restricted access, and the database will be locked only after completion of all data queries and quality checks.

